### 9.3.1 Primary endpoint

The primary endpoint is the comparison between groups of mean Griffiths III total score and sub-scores at 3 years. This criterion will be analysed using a Student's t test or a Mann-Whitney test in the case of a non-normal distribution. An additional regression analysis may be carried out to look for possible confounding factors such as (but not limited to): family environment, term of pregnancy, etc.

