## **4.3 Primary endpoint**

To demonstrate that screening for OSA by PSG and its treatment if necessary is associated with an improvement in neurocognitive development; the mean total score and sub-scores of the Griffiths III at the age of 3 years will be compared between the groups.

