## **9. STATISTICAL ANALYSIS**

### **9.1 Sample size calculation**

Sample size calculation is based on the expected results of the Griffiths III neurocognitive assessment test. The expected difference between the mean score of the *Screened Group* and the mean score of the *Standard Care Group* was defined empirically by the experts and set at 8 points. Ellis et al. report the results of a clinical study in children with DS in whom Griffiths III was conducted on subjects between the ages of 18 and 25 months. The standard deviation used to calculate the sample size was used for the present study. Although the version of the GMDS used in the Ellis et al. study is an earlier version than the one to be used in the present study, the experts considered that the variance should not be significantly impacted. A standard deviation of 11.55 was therefore used.

By setting the type I error at 5% and the type II error risk at 20%, 34 children must be included in each of the groups in order to be able to demonstrate a difference of at least 8 points between the two groups with a power of 80%. Assuming an attrition rate of 15% due to lost to follow-up or missing data, 40 patients per group should be included, for a total of 80 children. This sample size is compatible with the inclusion capacity based on incidence of DS and also the technical constraints imposed in performing PSG.

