### **9.3 Statistical analysis**

The statistical analysis will be carried out by CLINACT using SAS software version 9.2 or later. Statistical tests will be considered significant if the level of significance is less than 5% for all analyses. Comparisons will be bilateral.

The main statistical analysis will focus on the "intent-to-treat" (ITT) population. A second analysis will be carried out on the "per protocol" (PP) population in order to confirm the results of the analyses of the primary endpoint.

A statistical analysis plan will be drawn up once the protocol has been approved. This document will present an exhaustive list of the analyses that will be carried out and the statistical methods that will be applied. This document will be used as a reference for statistical analyses.

There will be a single analysis at the end of the study (final analysis).  
Missing data at the time of analysis will not be replaced and will be considered as such.  
Patients included, with an assessment of the primary endpoint, will be included in the "intent-to-treat" (ITT) population.  
ITT patients without major protocol deviations will be included in the "per protocol" (PP) population.  
These deviations will be defined before the database is frozen: for example, failure to comply with the protocol or the presence of an exclusion criterion.  
The safety analysis will be carried out on the Safety population (all patients included).

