#### **Griffiths III:**

Assessment of neuro-cognitive development using the Griffiths scale is the study primary endpoint.

This is a test that assesses the child's psychomotor development from birth to the age of 6 years. This test, previously known as the Griffiths Mental Development Scales, was revised and re-standardized on a significant sample of the British population and published in 2016.

The Griffiths III can be used to calculate a development global score, as well as to define the child's strengths and weaknesses in five areas (Foundation of learning, Language and communication, Eye and hand coordination, Personal-social-emotional and Gross motor coordination).

The gestational age, the adjustment for prematurity and the corrected age will be recorded in the e-CRF.

Will be recorded in the e-CRF:

- The raw score for section 1, section 2 and section 3 for children aged 3 years, and sections 4 and 5 for children aged 5 years for each of the five subscales;
- The developmental age corresponding to each subscale, expressed in months;
- The QD for each subscale according to the formula  $MA/RA \times 100$  (mental age/real age\*100);

Lastly, for the Global Quotient of Development (GQD), the following will be recorded:

- The total raw score (sum of the raw scores for the five subscales/5);
- The developmental age (in months);
- The score of GQD.

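### The Griffiths III total score and its five sub-scores are jointly primary with no decision rule, so the stated 5% error and 80% power cannot both hold

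*Protocol*

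**What the plan says.** Section 9.3.1 defines the endpoint: "The primary endpoint is the comparison between groups of mean Griffiths III total score and sub-scores at 3 years". Section 4.3 and the Endpoints row of the synopsis agree: the total score and the sub-scores "at the age of 3 years will be compared between the groups", with no order among them. Section 11.4.1 gives the number of sub-scores, describing a child's "strengths and weaknesses in five areas (Foundation of learning, Language and communication, Eye and hand coordination, Personal-social-emotional and Gross motor coordination").

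On testing, section 9.3 says: "Statistical tests will be considered significant if the level of significance is less than 5% for all analyses". It adds: "Comparisons will be bilateral". Section 9.3.1 names the test: "This criterion will be analysed using a Student's t test or a Mann-Whitney test in the case of a non-normal distribution".

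On size, section 9.1 takes an expected difference of 8 points in mean score and one standard deviation, 11.55. With 5% and 20% error risks it concludes that "34 children must be included in each of the groups in order to be able to demonstrate a difference of at least 8 points", then allows 15% attrition to reach 40 per group. No standard deviation or expected difference is given for any sub-score.

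On the scale, section 11.4.1 records three global quantities: "The total raw score (sum of the raw scores for the five subscales/5"), a developmental age in months, and the Global Quotient of Development (GQD). Sections 4.3, 9.1 and 9.3.1 do not say which one is the total score. The synopsis expresses the 8 points on the GMDS, also without naming a quantity.

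**The concern.** Three parts of the protocol do not fit together: an endpoint made of six comparisons, a 5% threshold applied to each, and a sample size for one. Because no rule turns six results into one conclusion, a reader cannot tell what would count as meeting the primary objective. The false-positive risk and the power of the trial's main claim both depend on that missing rule.

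The unnamed scale adds to this. The 8-point difference and the SD of 11.55 can describe only one of the three global quantities. By the quotient formula in section 11.4.1 (mental age divided by real age, times 100), at 36 months 8 quotient points equal 8/100 × 36 = 2.9 months of developmental age, while 8 months of developmental age equal 8/36 × 100 = 22 quotient points.

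**Working it through.** **Inputs from the protocol.** Difference 8, SD 11.55, two-sided 5%, power 80%, attrition 15% (sections 9.1 and 9.3); five sub-scores plus one total (section 11.4.1); Student's t test (section 9.3.1).

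**Step 1: reproduce the stated size, one comparison.**
- Normal approximation: n = 2 × [SD × (z₀.₉₇₅ + z₀.₈₀)/difference]² = 2 × [11.55 × (1.960 + 0.842)/8]² = 32.7, so 33 per group.
- With the t distribution: 33.7, so 34 per group, as stated. Power at 34 per group is 80.3%.
- Attrition: 34/0.85 = 40 per group, as stated.

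Section 9.1 is therefore correct for a single test.

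**Step 2: type I error if any one of six results suffices.** If all six tests were independent, it would be 1 − 0.95⁶ = 26.5%. This is an upper figure, because the total is built from the sub-scores. The more realistic set-up takes five sub-scores with a common correlation r and their mean as the total, 34 per group, no true effect, two-sided t tests at 5%, and 40,000 simulated trials per value of r. The values of r are assumptions, as the protocol gives none.

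| r | Chance that at least one of six is significant |
|---|---|
| 0 | 24% |
| 0.3 | 21% |
| 0.5 | 18% |
| 0.7 | 15% |
| 0.9 | 10% |

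The lower end of r is unlikely for sub-scales of one developmental test, but even r = 0.9 gives about twice the stated 5%.

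**Step 3: power if all six results must be significant.** Type I error then stays at or below 5%. Power was simulated with the same set-up, counting trials in which all six results are significant in favour of screening. A true effect of 8/11.55 = 0.69 SD on every sub-score is assumed.

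| r | Power, all six significant |
|---|---|
| 0 | 34% |
| 0.3 | 44% |
| 0.5 | 52% |
| 0.7 | 59% |
| 0.9 | 69% |

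This assumption favours the trial. If the 0.69 SD applies instead to the total, with equal shifts on the sub-scores, each sub-score effect is smaller in SD units. Power for all six is then 24% at r = 0.5 and 65% at r = 0.9.

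**Step 4: one primary score.** This is Step 1: 5% two-sided, 80.3% power, 34 evaluable and 40 included per group.

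**The case against.** The best defence is that one score was always meant. Section 9.1 speaks of a single mean score per group, section 11.4.1 describes one global score with five areas as a profile, and section 9.3.1 refers to the endpoint in the singular. Section 9.3 also leaves the list of analyses and the methods to a statistical analysis plan that is not shown here, and the order of tests is often set there. This supports the proposed fix, but it does not remove the conflict. Three places in the protocol give the sub-scores primary status. An analysis plan that named one primary score would contradict those places, and one that adjusted the level would contradict the 5% sentence in section 9.3.

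Four stronger readings are tempting, and the protocol does not support them.
- A reader might infer that one significant sub-score is enough to claim success. No such rule is written. The 10% to 24% error applies only if that rule were used.
- A reader might infer that the scale could be chosen once open-label results are visible. Section 9.3 has the analysis plan drawn up once the protocol is approved, and nothing shows the choice being held back.
- A reader might infer that the sample size is wrong. It is right for one test.
- A reader might extend the point to significance tests on the VABS-II, BRIEF-P and CBCL-P. These are secondary endpoints with their own objectives in section 4.2, and nothing here shows those tests to be wrong.

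The three global quantities can also be read as steps towards one GQD, since section 11.4.1 lists them under that heading. That makes the scale a matter of clarification, but sections 4.3, 9.1 and 9.3.1 should still name it.

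**Conclusion.** The concern holds. As written, the primary endpoint comprises six comparisons with no ranking and no decision rule, each at two-sided 5%, in a trial sized for one. The stated 5% and 80% do not both hold under either of the two obvious rules. If any one result suffices, the type I error is about 10% to 24%. If all six are required, power is about 34% to 69%. The first range rests on assumed equal correlations between sub-scores of 0.9 down to 0 and a total equal to their mean. The second uses the same correlations, running upward from 0 to 0.9, with 0.69 SD on every sub-score. The conclusion does not depend on the exact correlation within this range. It also does not depend on what the unseen analysis plan contains, because the protocol itself fixes both the endpoint and the threshold.

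**What to change.** 1. In the synopsis, section 4.3 and section 9.3.1, name one primary endpoint: the Griffiths III global score at 3 years, tested two-sided at 5%. State the quantity that carries the 8-point difference and SD of 11.55 (the GQD, if that is the scale meant), and name the same quantity in section 9.1.
2. Make the five sub-scale scores secondary, and state that they cannot support the primary claim on their own. One way is to test them only if the global score is significant.
3. Reword the sentence in section 9.3 that applies 5% to all analyses, so that it agrees with this order.

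The cost is wording in the protocol and the matching text in the analysis plan. The 34 evaluable and 40 included per group stand, and testing of the other secondary endpoints is unaffected. The one thing given up is the possibility of claiming primary success on a sub-score alone.

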| 
STATISTICAL
METHODOLOGY
 | 
Calculating the number of subjects
By setting the <math>\alpha</math> risk at 5% and the <math>\beta</math> risk at 20%, 34 children must be included in each of the groups in order to be able to demonstrate a difference of at least 8 points on the GMDS between the two groups with a power of 80%. Taking into account the 15% of patients lost to follow-up or missing data, 40 patients per group should be included, for a total of 80 children. The 8-point difference was set empirically by the experts.
 
Statistical analysis
Statistical analyses will be carried out using SAS software. The methodology used will be described exhaustively in a statistical analysis plan. The main statistical analysis will focus on the "intent-to-treat" (ITT) population. A second analysis will be carried out on the "per protocol" (PP) population in order to confirm the results of the analyses of the primary endpoint. The main analysis will be a comparison of the mean scores obtained on the Griffiths III scale using a Student's t-test (or Mann-Whitney test in the case of a non-normal distribution); an additional regression analysis will be carried out to look for confounding factors that could influence the Griffiths III scores (such as, but not limited to: family environment, term of pregnancy, etc.). For secondary analyses, quantitative variables will be analysed using a Student's t-test (or Mann-Whitney test in the case of a non-normal distribution) and qualitative variables using a Chi-squared test (or Fisher's exact test). To assess the predictive value of peripheral saturation and/or nocturnal transcutaneous carbon dioxide, and/or actigraphy and/or the suprasternal pressure sensor, an ROC curve analysis will be performed, with selection of the threshold values giving the best specificity and sensitivity.
 |

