## **7. CONDUCT OF THE STUDY**

### **7.1 Study methodology**

This is an interventional, comparative, multicentre, open-label, minimal-risk study without drug (Etude Hors Produit de Santé (HPS)).

The Institut Jérôme Lejeune (IJL) is the coordinating centre.

The IJL and the Necker-Enfants Malades Hospital are the investigating centres.

The planned duration of the inclusion period is 24 months; it may be modified if necessary, at the sponsor's discretion.

The children in the *Screened Group* will be monitored until they are 36 months old. Each PSG will be carried out within 1 month. An additional 3 months may be necessary if the PSG at home is unsuccessful (2 months between the 1st PSG and the 2nd PSG at home and 1 additional month between the 2nd PSG at home and the one carried out at the Necker - Enfants Malades Hospital). Children in the *Standard Care Group* will not be followed prospectively, and data concerning their medical follow-up, including PSG and treatment of OSA before the age of 3 years, will be collected in their medical records. Their PSG at the age of 3 years will be carried out within 1 month. An additional delay of 3 months may be necessary if the PSG at home is unsuccessful (2 months between the 1st PSG and the 2nd PSG at home and 1 additional month between the 2nd PSG at home and the one carried out at the Necker - Enfants Malades Hospital).

The expected duration of the research is 5 years + 4 months maximum.

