### **7.2 Patients' recruitment**

The parents or legal representatives of children with DS will be contacted by telephone by the Institute's investigators to ask them to take part in the study. The ICF will be sent to them by post or email, allowing them a reasonable period of reflection between the telephone contact and the inclusion visit.

This same ICF will be presented orally by the investigator during the inclusion consultation at the IJL. Participation in the study will be offered to all infants under 6 months and all children aged 36  $\pm$  1 months, and the two groups will be recruited in parallel. Children who meet the eligibility criteria and whose parents or legal representatives sign the ICF after a sufficient period of reflection will be included. A copy of the ICF, dated and signed, will be given to those holding parental authority. The investigator will keep the original.

Children aged less than 6 months will form the *Screened Group*, and children aged 36  $\pm$  1 months the *Standard Care Group*.

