#### Children in the *Standard Care Group*:

- They will be seen at a consultation during which they will undergo a neurocognitive and behavioural assessment at 3 years of age.
- They will receive PSG at home (or at the sleep unit at Necker-Enfants Malades Hospital if PSG at home is unsuccessful twice).
- These children will not be monitored prospectively and their medical follow-up before the age of 3 will be collected from their medical records. This includes potential screening and treatment for OSA.

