As the primary endpoint involves tests to assess neurocognitive and behavioural development, we will also monitor all neurological events, which are confounding factors in children's intellectual disability and may influence the primary endpoint.

AEs and serious AEs linked to the ENT (otitis, angina, rhinitis, pneumopathy, other), neurological and cardiopulmonary systems will also be reported in the e-CRF and to the sponsor. Initiating antibiotic treatment or hearing aid fittings should also be recorded.

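### Groups are formed by age, not by randomisation, yet the protocol fixes an unadjusted test as the main analysis and leaves confounder adjustment as a loosely defined extra

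*Protocol*

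**What the plan says.** Protocol section 7.1 describes the design: "This is an interventional, comparative, multicentre, open-label, minimal-risk study without drug". Randomisation and matching are mentioned nowhere. Under section 7.2, infants under 6 months become the Screened Group and children of 36 ± 1 months become the Standard Care Group, recruited in parallel.

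Section 7.3 gives the Screened Group four visits, six PSGs and a telephone call every two months. The Standard Care Group has one assessment at age 3, and of these children it says: "These children will not be monitored prospectively and their medical follow-up before the age of 3 will be collected from their medical records".

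On the main analysis, the synopsis states: "The main analysis will be a comparison of the mean scores obtained on the Griffiths III scale using a Student's t-test", with Mann-Whitney as the alternative for non-normal data. Section 9.3.1 agrees: "This criterion will be analysed using a Student's t test or a Mann-Whitney test in the case of a non-normal distribution".

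On adjustment, the two places differ. The synopsis says "an additional regression analysis will be carried out to look for confounding factors that could influence the Griffiths III scores". Section 9.3.1 says "An additional regression analysis may be carried out to look for possible confounding factors such as (but not limited to): family environment". In both, the regression is additional to the main test and its list of factors is open-ended.

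Section 8.1 accepts that confounding is a live issue for this endpoint. It plans to monitor "neurological events, which are confounding factors in children's intellectual disability and may influence the primary endpoint".

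**The concern.** Without randomisation, nothing in the design makes the groups comparable in expectation. Three features could separate them apart from screening:

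- **Birth cohort.** Parallel recruitment at 0–6 months and at 36 months means the children were born roughly 2.5 to 3 years apart.
- **Volunteering.** Agreeing to three years of repeated PSG is a different commitment from agreeing to one assessment.
- **Timing of eligibility.** The same criteria, such as expected ability to take the Griffiths test and no previous CPAP, are judged in early infancy in one group and at age 3 in the other.

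The test on which the main conclusion rests ignores all of this. The regression does not repair it as planned: it is described as a search for confounders rather than as the estimate of the group effect, its covariates are not fixed, and the protocol is inconsistent on whether it will be run. An adjusted result chosen after seeing the data would carry little weight beside a declared unadjusted main result.

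**Working it through.** **1. The plan's own figure.** Inputs from section 9.1, with two-sided testing from section 9.3: difference 8 points, SD 11.55, type I error 5%, power 80%. The noncentral t calculation gives 33.7, so 34 per group, with power 80.3%. Allowing for 15% attrition, 34 / 0.85 = 40 per group. The stated 34 and 40 reproduce. The calculation assumes that the groups differ only through screening.

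**2. Effect of confounding on the unadjusted test.** With 34 per group:

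- SE of the difference = 11.55 × √(2/34) = 2.80 points.
- Critical t on 66 df = 1.997, so an observed difference of about 1.997 × 2.80 = 5.6 points is significant.
- If screening has no effect but confounding shifts the mean difference by b, the t statistic has noncentrality b / 2.80.

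| Assumed shift b (points) | Noncentrality | Probability of p < 0.05 |
|---|---|---|
| 0 | 0 | 5% |
| 2 | 0.71 | 10.8% |
| 3 | 1.07 | 18.4% |
| 4 | 1.43 | 29.1% |

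The shifts are assumptions. To judge whether they are plausible, take one covariate with correlation ρ to the score and a between-group imbalance of d SD. The shift is then about ρ × d × 11.55:

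- ρ = 0.3, d = 0.5: 1.7 points
- ρ = 0.5, d = 0.5: 2.9 points
- ρ = 0.5, d = 0.75: 4.3 points

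Moderate confounding is enough.

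**3. Does adjustment cost or gain power?** Assume that covariates explain 20% of the variance, so the residual SD is 11.55 × √0.8 = 10.33. For k independent covariates, each imbalanced by d SD between equal groups, the variance inflation is 1 + k·d²/4. Power at 8 points with 34 per group:

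| Scenario (assumed) | Variance inflation | Effective SD | Power |
|---|---|---|---|
| Covariates balanced | 1 | 10.33 | about 88% |
| Six, each imbalanced by 0.25 SD | 1.094 | 10.80 | about 85% |
| Six, each imbalanced by 0.5 SD | 1.375 | 12.11 | about 76% |
| Unadjusted test | – | 11.55 | 80% |

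Six covariates reduce the residual df from 66 to 60, which changes these powers by only about 0.1 percentage point.

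**4. The choice between t-test and Mann-Whitney.** A simulation of the two-stage procedure under no effect (34 per group, switching to Mann-Whitney when Shapiro-Wilk is significant at 5% in either group, 10,000 runs) gave a type I error of 4.9% for normal and for lognormal data. The switch does not inflate false positives. What remains is that the endpoint and the 8 points are differences in means, which a Mann-Whitney test does not estimate.

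**The case against.** **Shared restrictions.** Both groups face the same entry criteria: gestational age of at least 36 weeks, non-mosaic trisomy, no listed neurological disease or leukaemia, a predominantly French-speaking home, residence in the Paris area and expected ability to take the Griffiths test. Section 7.2 offers the study to all infants under 6 months and all children of 36 ± 1 months. This narrows the scope for confounding but does not remove it. It does mean that prognosis *may* differ; the documents do not show that it does.

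**The objective is worded as an association.** A reader might infer that the main objective could not be answered at all. Section 4.1 does not support that: it asks whether screening is associated with better development, and an unadjusted comparison does estimate an association. What it cannot do is attribute the difference to screening.

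**The SAP can supply detail.** Section 9.3 promises an exhaustive SAP, and an exact covariate list belongs there. That answers the missing detail but not the main point. The protocol itself names the unadjusted test as the main analysis, so making the adjusted estimate primary needs a protocol change.

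**Two further inferences fail.** One is that adjustment would raise power to 88%. That figure requires covariates balanced between the groups, in which case they would not be confounding. The other is that the switch to Mann-Whitney is a serious fault. Its type I error cost is negligible, and the protocol uses it only for non-normal data, where a rank test can be the more powerful one.

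**Regression has limits.** Birth variables do not measure family motivation, and no covariate set removes birth-cohort or eligibility-timing differences. This stands. It is a reason for a modest conclusion, not for leaving the main analysis unadjusted.

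**Conclusion.** The point holds and should be fixed before outcome data are reviewed. The protocol rests its main conclusion on an unadjusted comparison of two groups formed by age, and contradicts itself on whether the supplementary regression will be run. A significant result could not be credited to screening. At the planned 34 evaluable children per group and SD 11.55, assumed confounding shifts of 2, 3 or 4 points raise the chance of a false significant result from 5% to about 11%, 18% or 29%. The true size and direction of any confounding are unknown.

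The case for adjustment is bias alone. If covariates explain 20% of the variance (assumption), power runs from about 88% to about 76% across the imbalances examined, against 80% unadjusted. The Mann-Whitney issue is minor and concerns only which quantity is estimated.

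**What to change.** 1. Make the primary analysis one linear regression of the Griffiths III total score (GQD) on group plus a short covariate list, and report the adjusted mean difference with its 95% CI whatever the distribution.
2. Choose covariates set at or before birth and recorded for both groups, fixed before outcome data are reviewed. Gestational age, birth weight, timing of the Down syndrome diagnosis and malformations (hence cardiac malformation) are in the inclusion-visit list of section 7.3.1; section 7.3.9 combines that visit with the 3-year visit for the Standard Care Group. Sex is a natural addition, but that list does not name it, so confirm that it is captured under patient characteristics.
3. Keep the unadjusted test as a sensitivity analysis.
4. Reconcile the synopsis and section 9.3.1 in favour of a firm commitment, and drop the aim of looking for confounders.
5. Family environment is the first confounder the protocol names, but socio-professional category is scheduled only at the 5-year visit of screened and treated children (sections 2.3 and 7.3.11). Include it only if it can be obtained for all children at 3 years.
6. State that regression cannot remove birth-cohort, volunteer or eligibility-timing differences, and word the conclusion as an association.

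**Cost.** Protocol and SAP wording, about 6 of 66 degrees of freedom, and possibly slightly lower power if covariates are imbalanced. Socio-professional category would be a new data item at 3 years, and the synopsis calendar ends the main patient follow-up in September 2022, so it may have to be collected retrospectively. The other items need no change to the sample size or visits.
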